### Blinding

The nature of acupotomy means that patients and acupotomy doctors cannot be blinded during the treatment. Outcome assessors and statisticians will be blinded to group assignments. In this study, acupotomy doctor, outcome assessors, and statisticians will be independent.

### Interventions

Patients in both groups will be prescribed diclofenac diethylamine emulgel (Voltalin, 1 g emulgel contains the main ingredient dichlorophenic acid diethylamine 10 mg, Beijing Novartis Pharma Ltd) of 3–4 times per day. A proper amount of diclofenac diethylamine emulgel will be applied according to the size of the knee pain area, then a gentle rub will be needed to make it penetrate the skin. The course of treatment will be 4 weeks. And each patient will be given a diary to keep track of how many times they used Voltalin each day. During the study period, loxoprofen sodium tablets (Loxonin, Dachi Sankyo Pharma Ltd) will be provided as rescue medication in case of intolerable knee pain, with the usage documented by the outcome assessors. Besides, all other interventions, such as acupuncture, moxibustion, physical therapy, surgical procedures, and intra-articular injections for KOA, will be forbidden. Other medications that do not influence pain will be allowed.

The patients in the acupotomy group will receive acupotomy in the hospital one time per week for 4 weeks. A sterilized, disposable needle-scalpel (Hanzhang No.4, length: 60 mm, diameter: 0.6 mm, Beijing Hanzhang Medical Device Co., Ltd) will be used. To keep the consistency and standardization of the operation, the acupotomy will be performed by an experienced doctor who has a Chinese medicine practitioner license and has been qualified for at least 15 years according to the basic operating procedures of acupotomy in the *Principles of Acupotomy*. The appropriate body position will be chosen depending on the location of the operation, such as supine, prone or side-lying position. The medial collateral ligaments, lateral collateral ligaments, hamstring muscle, quadriceps femoris, iliotibial band, popliteus muscle, anserine bursa, subpatellar fat pad, and the peripatellar area will be touched and pressed, then the spots with induration and cordlike tissue will be identified as positive points. Generally, 5–7 positive points will be selected in light of the specific pain sites, functional limitations, and imaging examination results of the patients’ joints. The selected points will be marked with gentian violet, and then the surrounding skin will be disinfected with iodophor. After sterile skin preparation, a needle-scalpel will penetrate the skin and gradually go deeper. When feeling a sense of toughness or resistance under the needle-scalpel, the manipulation of acupotomy is performed. After treatment completion, the doctor will check for any abnormality and bleeding, then apply the Band-Aid to the pinhole.

### Outcomes

If only one knee meets the ACR criteria and Kellgren-Lawrence grade II to IV, then this knee will be evaluated. When both knees are in accordance with the inclusion criteria (ACR and Kellgren–Lawrence grade II to IV), the more painful knee will be chosen for assessment. Figure 2 shows the treatment and outcome measurement schedules.

**Fig. 2 Fig2:**
[figure not shown]
Treatment and outcome measurement schedules during the study, NSAIDs, nonsteroidal anti-inflammatory drugs; WOMAC, Western Ontario and McMaster Universities Osteoarthritis Index; SF-12, 12-item Short-Form Health Survey

### Primary outcome measurement

The primary outcome will be the response rate. The response rate is the percentage of patients with improvement in average pain NRS of at least 2 points [24], which is regarded as a minimum clinically important difference, and in the Western Ontario and McMaster Universities Osteoarthritis Index (WOMAC) [25] function subscale score of at least 6 points [24] at week 4 compared with baseline. The NRS is a digital scale using “0” to “10” to indicate the severity of the average pain over the last week, with “0” representing painless and “10” representing the most severe pain. The WOMAC function subscale (Likert version 3.1) consists of 17 questions (each scored from 0 to 4) relating to the difficulty experienced due to knee osteoarthritis, with higher scores referring to poorer knee function.

### Secondary outcome measurements

The NRS and WOMAC pain subscale will be used to measure the average pain over the last week at weeks 0, 4, 8, and 24. WOMAC pain subscale ranges from 0 to 20. It has five items assessing the severity of pain in five different conditions, with higher scores indicating worse pain.

The WOMAC function subscale will be used to measure the physical function at weeks 0, 4, 8, and 24. The WOMAC function subscale ranges from 0 to 68 and includes 17 items, with lower scores indicating better function.

The WOMAC stiffness subscale will be used to measure the degree of stiffness of the knee at weeks 0, 4, 8, and 24. The WOMAC stiffness subscale ranges from 0 to 8 and includes two items, with higher scores indicating more stiffness.

The 12-item Short-Form Health Survey (SF-12) [26] will be used to assess the quality of life at weeks 0, 4, 8, and 20. SF-12 includes the mental and physical domains. Each domain ranges from 0 to 100, with higher scores indicating a better quality of life.

The use of rescue medicine (loxoprofen sodium tablets) will also be recorded throughout the trial.

### Laboratory outcome measurement

Joint fluid and venous serum will be collected at week 0 and week 4, and the levels of tumor necrosis factor-α (TNF-α), interleukin-1β (IL-1β), and matrix metalloproteinase-3 (MMP-3) will be tested.

### Adverse events

All adverse events will be recorded throughout the trial by researchers using a record book, which consists of the time, severity, and duration of the adverse event, the disposition taken, and the prognosis of the event. Serious adverse events refer to events that require hospitalization or prolonged hospitalization, disability, affect work ability, or threaten life or death during the clinical trial. If serious adverse events occur, the clinical trial should be withdrawn and appropriate treatment measures should be taken immediately for the subjects. However, according to long-term clinical observation, we have not found the occurrence of serious adverse events caused by acupotomy. Common treatment-related adverse events include bleeding, subcutaneous hematoma, infection, continuous post-needling pain, dizziness, and syncope [27].

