**Methods/design:**

This is a parallel-group, assessor-blinded randomized controlled trial. Two hundred patients with KOA will be recruited and randomly assigned to two groups (group A or group D) in a 1:1 ratio. Patients in group A will receive acupotomy and topical diclofenac diethylamine for 4 weeks, while patients in group D will receive topical diclofenac diethylamine alone for 4 weeks. The primary outcome will be the response rate—the proportion of patients who achieve the minimal clinically important improvement in pain and function at week 4 compared with baseline. Secondary outcomes will include pain, function, quality of life, the use of rescue medicine (loxoprofen sodium), and adverse events at weeks 4, 8, and 24 after randomization. Besides, joint fluid and serum will be collected to assess the level of inflammatory cytokines, like TNF-α, IL-1β, and MMP-3.

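### Adverse events: weekly contact in weeks 1–4 is described only for group A and no matching enquiry is stated for group D, so the safety comparison is open to detection bias of unknown size

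*Protocol article*

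**What the plan says.** **Group A.** The Interventions section states: "The patients in the acupotomy group will receive acupotomy in the hospital one time per week for 4 weeks". It also describes what happens at each session: "After treatment completion, the doctor will check for any abnormality and bleeding, then apply the Band-Aid to the pinhole". The Blinding section confirms that this doctor cannot be blinded.

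**Group D.** According to the abstract, "patients in group D will receive topical diclofenac diethylamine alone for 4 weeks". No weekly visit is described. The dated assessments in the Outcomes sections fall at weeks 0, 4, 8 and 24 (the SF-12 is printed with week 20 as its last time point).

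**Both arms.** The Adverse events section states: "All adverse events will be recorded throughout the trial by researchers using a record book". The abstract's list of secondary outcomes ends "and adverse events at weeks 4, 8, and 24 after randomization". On the diary, the Interventions section says that "each patient will be given a diary to keep track of how many times they used Voltalin each day". The Quality section promises regular follow-up, with dates set by a study calendar. It gives compliance as the purpose and states no frequency. Rescue-drug use is documented by the outcome assessors throughout the trial. The schedule itself is in Fig. 2, which is not reproduced in the text available here.

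**Aim.** The Objectives section makes safety, compared between the two arms, part of the study's purpose.

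**The concern.** When researchers write events into a record book, an event enters the data only if a researcher learns of it. A patient who comes to hospital every week can mention dizziness, a skin reaction or stomach upset within days. A patient who is first asked at week 4 has to recall the same event up to four weeks later.

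Both arms use the same gel and have access to the same rescue drug, so events caused by these should balance between the arms. They balance in the recorded data only if they are looked for equally. If they are not, background events are added to the real procedural harms in group A, and acupotomy looks less safe than it is. No later analysis can restore events that were never recorded, so this has to be settled in data collection and not in the analysis plan. The primary outcome is not affected.

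**Working it through.** The plan gives no figure on this point to reproduce. The check has two parts.

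**1. Contacts described for weeks 0–4**

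| Source of information | Group A | Group D |
|---|---|---|
| Hospital sessions (Interventions) | 4, one per week | none described |
| Check after the session (Interventions) | yes, by an unblinded doctor | not applicable |
| Regular follow-up (Quality) | yes; frequency not given; for compliance | same |
| Diary (Interventions) | gel applications only | same |
| Rescue-drug record (Interventions) | drug use; timing not given | same |
| Dated adverse-event outcome (abstract) | week 4 | week 4 |

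The shared rows neither create nor remove an imbalance. The difference lies in the first two rows. The session days are not stated. If sessions fall at weeks 0, 1, 2 and 3, the first has no exposure before it. If they fall at weeks 1, 2, 3 and 4, the last coincides with the week-4 assessment. Either way, 4 − 1 = 3 interim contacts bear on non-procedural events in group A, and none with a stated date does so in group D.

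**2. What unequal detection could do (illustration only)**

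Inputs:
- n = 100 per arm, from the Sample size section.
- True risk r of a mild event, equal in both arms: assumed 10%, 20% or 30%.
- Detection probability: assumed d_A = 90% in group A, and d_D = 90%, 70% or 50% in group D.

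Formulas:
- Recorded risk p = r × d in each arm.
- Risk ratio = p_A / p_D = d_A / d_D, which does not depend on r.
- False-positive rate = the chance that a two-sided 5% normal test of p_A against p_D rejects, although the true risks are equal.

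Worked case, r = 20%: 0.20 × 0.90 = 18% in A; 0.20 × 0.70 = 14% or 0.20 × 0.50 = 10% in D. The differences are 4 and 8 percentage points, and the risk ratios are 0.90/0.70 = 1.29 and 0.90/0.50 = 1.80.

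| True risk | Detection A / D | Recorded A / D | Difference (points) | Risk ratio | False-positive rate |
|---|---|---|---|---|---|
| 10% | 90% / 70% | 9% / 7% | 2 | 1.29 | 8.1% |
| 10% | 90% / 50% | 9% / 5% | 4 | 1.80 | 19.8% |
| 20% | 90% / 70% | 18% / 14% | 4 | 1.29 | 12.0% |
| 20% | 90% / 50% | 18% / 10% | 8 | 1.80 | 37.0% |
| 30% | 90% / 70% | 27% / 21% | 6 | 1.29 | 16.8% |
| 30% | 90% / 50% | 27% / 15% | 12 | 1.80 | 55.0% |
| any of these | 90% / 90% | equal | 0 | 1.00 | 5% |

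The last row matters as much as the others, because the article does not rule out equal detection.

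**The case against.** The strongest reply is that this rests on silence in a condensed article. Recording is promised for the whole trial in both arms, follow-up is promised by calendar, and rescue use is tracked throughout. In group D the only study treatment is four weeks of gel, so compliance follow-up there may well fall inside weeks 1–4. Fig. 2 or the full protocol may set out equal contact. This stands as far as it goes. A reader might infer that group D has no contact at all until week 4, and the text does not support that. What the text lacks is a stated frequency, and any statement that these contacts include a question about adverse events.

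A second reply is that the check after each session is aftercare. It mainly finds puncture-site problems, which group D cannot have. That also stands: the check is weak evidence of unequal detection for shared events. The weekly attendance is the stronger evidence.

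Third, most of the common events that the article lists (bleeding, hematoma, infection, post-needling pain) come largely from the procedure, so an excess in group A would be partly real. This is correct, and it is a reason to report the two kinds of event separately.

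Fourth, the rates in the illustration have no source in the article. They show a mechanism and are not an estimate.

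**Conclusion.** The point holds in a limited form. The text describes weekly contact for one arm only and states no common adverse-event enquiry that would offset it. The safety comparison is therefore open to detection bias, mainly for mild, short-lived events that can occur in both arms, such as dizziness.

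A reader might go further and conclude that events will be found more often in group A and that the comparison is biased. The documents do not establish that. The direction is a reasonable inference from the contact pattern. The size is unknown: under the assumed inputs the spurious difference runs from 0 points with equal detection to 12 points in the most extreme case. Nor does it follow that procedural harms and background events cannot be told apart, since many procedural events are recognisable by their nature.

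This is a moderate point with a cheap remedy. If Fig. 2 or the full protocol already sets the same enquiry at the same times in both arms, one sentence saying so would settle the question of contact and leave only the separate reporting.

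**What to change.** 1. Add an adverse-event line (date, event, duration) to the diary that every patient already keeps.
2. Ask the same scripted open question about adverse events at the same time points in both arms: within the existing compliance follow-up, with its frequency stated, and at weeks 4, 8 and 24. A researcher other than the blinded outcome assessor should ask it, because the answers can reveal the group.
3. Report procedure-only events (bleeding, hematoma, post-needling pain) separately from events that can occur in both arms. Base the between-arm comparison on the latter, as collected by the common method. Still record and list events that come to light only at an acupotomy session, marked with that source.

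**Cost.** The diary becomes slightly longer and the follow-up contacts a little fuller; no extra staff are needed. Recruitment began on March 25, 2021, so patients already enrolled will have been asked differently. The date of the change must be recorded, so that the safety results can be shown before and after it.

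Weekly telephone calls to group D are optional. They would match the contact more closely, but would mean 100 × 4 = 400 calls and would change the attention given to group D in an open-label trial with a patient-reported primary outcome.

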### Data monitoring and auditing

The case report form (CRF) will be completed in paper form by a data entry operator (DEO) and then entered into an Excel spreadsheet by two electronic data interchange (EDI) administrators independently to ensure the accuracy of the data. The researchers will keep all trial data, including signed informed consent, CRF, and operation procedure records. The results of this study may be published in a peer-review medical journal, but we will not disclose the privacy of patients. The research supervision department, the ethics committee of the hospital, and its relevant personnel will audit the trial per year.

### Quality

Before the inclusion of patients, all the researchers will be trained on the implementation program, including scale evaluation, data measurement, and CRF filling. A special quality examiner will be set up to check the quality of the research regularly. The CRF should be strictly managed, and the researchers should truthfully, meticulously record as required to ensure that the contents of the CRF are reliable and completed. Regular follow-up will be conducted to ensure the compliance of patients during the study, and the drop-out rate should be controlled within 20%. A study calendar will be used to determine the exact time point for follow-up. Moreover, all treatments, acupotomy, diclofenac diethylamine emulgel, and loxoprofen sodium, will be provided for patients for free.

### Protocol amendments

If the protocol amendments occur during the implementation of the study, researchers will communicate the important protocol changes and report changes to the ethics committee. And CRFs will be updated timely to record all the first-hand clinical trial data of the patients.

### Sample size

The primary outcome in this study is the response rate, and the allocation ratio between the two groups is 1:1. A bilateral difference test will be used to calculate the sample size. According to a previous review, the response rate of the diclofenac diethylamine emulgel for KOA is assumed to be 60% [28]. The response rate in the acupotomy group is assumed to be 80% based on preliminary clinical experience. The sample size of each group is 80 calculated by PASS 11.0.7 (NCSS, LLC, USA) software with a two-sided significance level of 5% and power of 80%. Considering a 20% drop-out rate, the final sample size of each group will be 100, with a total of 200.

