### Statistical analysis

SPSS 19.0 software will be used. For all statistical tests, *P* < 0.05 will be considered to be statistically significant. Continuous data will be presented as mean ± standard deviation (M±SD), while dichotomous data will be presented as a proportion. The independent sample *t* test or *χ*^2^ test will be used to compare demographic data and other baseline indicators to measure the equilibria between the two groups.

Covariance analysis will be used for continuous data and logistic regression analysis will be used for dichotomous data, which will be adjusted according to baseline and dosages of loxoprofen sodium. The results will be presented as mean difference or odds ratio, providing a 95% confidence interval (CI). Intention to treat analysis (ITT) will be carried out for all the randomized patients. The last observation carried forward (LOCF) method and the maximum likelihood regression will be used for the missing data of primary outcome.

The per-protocol (PP) set will include only those who complete at least three sessions and all planned follow-ups and have no major protocol violations (taking other drugs during the trial, etc.). The ITT set will be used for primary analysis, and the PP set will be used as in the sensitivity analysis.

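### The 20% drop-out allowance assumes drop-outs leave the analysis; if LOCF leads the primary ITT analysis they stay in as non-responders, and power at the planned loss is about 63%, not 80%

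*Protocol article*

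**What the plan says.** The Sample size section of the protocol article gives all the design inputs. For the control arm, "the response rate of the diclofenac diethylamine emulgel for KOA is assumed to be 60"%. For the other arm, "The response rate in the acupotomy group is assumed to be 80% based on preliminary clinical experience". It states that "the allocation ratio between the two groups is 1:1", and the calculation is made "with a two-sided significance level of 5% and power of 80"%. The result is: "The sample size of each group is 80 calculated by PASS 11.0.7". The attrition step follows: "Considering a 20% drop-out rate, the final sample size of each group will be 100, with a total of 200".

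The Statistical analysis section applies ITT to everyone randomized and adds: "The ITT set will be used for primary analysis, and the PP set will be used as in the sensitivity analysis". On missing data it says: "The last observation carried forward (LOCF) method and the maximum likelihood regression will be used for the missing data of primary outcome". It does not say which of the two methods leads.

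The primary outcome section defines response as an improvement from baseline to week 4 of at least 2 points on the pain NRS and at least 6 points on WOMAC function. The secondary outcome section schedules both scales at weeks 0, 4, 8 and 24.

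**The concern.** The two sections treat the same patients differently. The sample-size step removes 20% of each arm and relies on the 80 who remain. An ITT analysis with LOCF keeps all 100 and fills the gaps.

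The schedule determines what LOCF fills in. The only value before week 4 is baseline, so a patient with no week-4 assessment has a change of zero on both scales, misses both thresholds and counts as a non-responder. The article never uses that term; it follows from the visit times. Coding the same share of each arm as failures shrinks the difference between arms, and the extra 20 patients per arm do not make up for it.

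The stake is how a null result would be read. If LOCF leads and loss reaches the planned level, a non-significant result would be judged against a stated 80% power when the chance of missing the planned effect is more than one in three.

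**Working it through.** **Inputs.** From Sample size: p_D = 0.60, p_A = 0.80, two-sided 5%, power 80%, 1:1 allocation, 80 per arm before and 100 per arm after a 20% drop-out allowance. From the outcome sections: assessments at weeks 0, 4, 8 and 24, with the primary endpoint at week 4.

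**1. The plan's own figures.** The pooled two-proportion formula is

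n = [1.96·√(2p̄(1−p̄)) + 0.842·√(p_D(1−p_D) + p_A(1−p_A))]² / (p_A − p_D)².

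With p̄ = 0.70 the two roots are 0.648 and 0.632, so n = (1.270 + 0.532)² / 0.04 ≈ 81.2. The unpooled form gives 79 and the arcsine form 80.3. At 80 per arm, power is 79.4% by normal approximation and 80.1% by exact enumeration of the uncorrected chi-square test. The 80 is reproduced. The allowance is 80/(1 − 0.20) = 100, also reproduced.

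**2. Response rates under LOCF.** Let a share d of each arm be lost before week 4, and let 60% and 80% apply to the rest. Everyone lost counts as a non-responder, so the rates become 0.60(1−d) and 0.80(1−d). At d = 0.20 they are 0.48 and 0.64, and the difference falls from 20 to 16 points.

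**3. Power at 100 per arm.**

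Power = Φ{[|difference|·√n − 1.96·√(2p̄(1−p̄))] / √(p_D(1−p_D) + p_A(1−p_A))}.

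At 0.48 and 0.64, p̄ = 0.56 and the two roots are 0.702 and 0.693. The argument is (0.16 × 10 − 1.96 × 0.702)/0.693 = (1.600 − 1.376)/0.693 ≈ 0.323, so power is 62.7%. Exact enumeration gives 64.2%.

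| Lost before week 4, each arm | Rates D / A | Power at 100 per arm |
|---|---|---|
| 0% | 60% / 80% | 87.6% |
| 5% | 57% / 76% | 81.7% |
| 10% | 54% / 72% | 75.4% |
| 15% | 51% / 68% | 69.0% |
| 20% | 48% / 64% | 62.7% |

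At 6.5% loss the rates are 56.1% and 74.8% and power is 79.9%, so the 80% claim fails from about that point.

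**4. If the likelihood method leads.** A drop-out with no week-4 value adds essentially no information on response. At 20% loss about 80 per arm inform the comparison at 60% and 80%, which returns the 79–80% of step 1.

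**5. Scale of the gap.** Full 80% power at 48% versus 64% would need 150 per arm. This shows the size of the mismatch and is not a recommendation.

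**6. Unequal loss.** Under LOCF, 15% lost in D and 25% in A gives rates of 51% and 60% and power of 25%. The reverse, 25% in D and 15% in A, gives 45% and 68% and power of 91%.

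**The case against.** A reader might infer that the trial simply does not have 80% power and that 63% is the true figure. The document does not support that, for five reasons.

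- **Two methods are named.** The missing-data sentence gives maximum likelihood regression beside LOCF, without precedence. If it leads, the claim roughly holds. An analysis plan not seen here may settle the order. This objection stands, and the 63% must be stated as conditional on LOCF.
- **The 20% is not dated.** The Quality section treats 20% as a ceiling on drop-out, in the context of follow-up visits that run to week 24. Patients lost after week 4 have an observed primary outcome. This stands in part: the Sample size section applies the 20% to a week-4 endpoint, so the calculation itself treats it as week-4 loss, and half that loss still leaves only 75%.
- **60% and 80% may already count drop-outs as failures.** Power at 100 per arm would then be about 88%. The document cannot rule this out, but the inflation from 80 to 100 would then serve no purpose, so completer rates are the more natural reading.
- **Equal loss is assumed.** The plan gives one rate for both arms. Step 6 shows how far the LOCF figure moves otherwise.
- **The planned model is adjusted.** The article specifies logistic regression adjusted for baseline and loxoprofen dosage, whereas the figures here are for an unadjusted comparison of proportions. They compare like with like against the plan's own unadjusted calculation, but they are not the exact power of the planned model.

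It is also fair to say that lower power does not by itself bias the estimate, and that a 95% confidence interval is planned.

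**Conclusion.** The concern holds as a mismatch between the drop-out allowance and one of the two methods named for the primary outcome. It is not an arithmetic error: 80 and 100 per arm are both right for an analysis that leaves drop-outs out.

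The conditional size is about 63% power at 20% loss, against 80% stated. It rests on LOCF leading, the full 20% being lost before week 4, equal loss in the two arms, completer response rates and an unadjusted test. Under the same conditions the shortfall begins at about 6.5% loss, well inside what the plan allows for. With the likelihood method in the lead, and drop-outs adding no information, there is no material shortfall. The stated 80% therefore depends on a choice that the article leaves open.

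**What to change.** Choose one of two routes before any unblinded comparison.

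1. **Preferred.** Name the likelihood method, or multiple imputation, as the primary handling of a missing week-4 response, and keep baseline carried forward as a sensitivity analysis. The sizing for 80 observed patients per arm then roughly supports the 80% claim at 20% loss.
2. **If LOCF stays primary.** State that drop-outs before week 4 count as non-responders, and restate the power at 100 per arm as about 63% at 20% loss and about 75% at 10%, with the assumptions of equal loss and completer rates given.

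Neither route needs more patients or visits. The first costs slightly more analysis work and a statement of the missing-data assumption. The second costs a less favourable power figure.
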